### Statistical analysis

2.8

The software package R (version 3.0.1, “R & R” of the Statistics Department of the University of Auckland, Auckland, New Zealand) or STATA version 13.1 (StataCorp, College Station, TX, USA) will be used for the statistical analyses. To ensure sensitivity analyses, analyses of the primary and secondary outcomes will be conducted on the full analysis set (FAS) and per protocol set (PP). The last observation carried forward (LOCF) method will be used to impute the missing data.

Baseline characteristics will be presented using the t-test or Wilcoxon rank-sum test for continuous outcomes, and the chi-square test or Fisher's exact test for categorical outcomes. The differences in the intergroup comparisons of the means will be processed with the least squared mean (LSM) and the standard deviation, and the intragroup comparisons of the mean values will be analyzed with a repeated-measures ANOVA (RMANOVA) or a linear mixed-effects model analysis (LME). *P* < 0.05 will be considered statistically significant. The time point difference in contrast with the baseline will be examined with Dunnett's test.

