**Methods/design::**

This study protocol is for a prospective matched case-control study. A total of 84 participants will be recruited, 56 patients with hemiplia caused by stroke, and 28 control patients matched by age, gender, and body mass index. The primary outcome of this study will be the differences and changes in the radial augmentation index.

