#### Sample size

2.4.4

The sample size calculation was based on the 2010 age (50 years or older) and gender distribution data provided by the Korean Statistical Information Service (kosis.kr). The incidence rates of obesity and stroke were estimated according to the National Nutrition Survey conducted and released in 2014. The stratification variables were as follows: age (A_1_: 50–69 years; A_2_: 70 years or older), gender (S_1_: male; S_2_: female), and obesity status (O_1_: BMI < 25 kg/m^2^, O_2_: BMI ≥ 25 kg/m^2^). A total of 8 cells (strata) were created based on combinations of the 3 variables. The frequencies of the stratification variables in each cell are shown in the table.

The Neyman allocation method was used, and the sample size was calculated with a confidence interval of 95% (α=0.05) and a margin of error of Є=10% following equation was used to calculate the total sample size and the sample size for each stratum:^[8]^ 

 

*N* refers to the total number of stroke patients in the corresponding age group, *N*_*i*_ to the size of the *i* stratum of the patient group, *n*_+_ to the sample size of the patient group, *p*_+_ to the population ratio of the *i* stratum, z_α/2_ to the top 100 (α/2)% quantile in a standard normal distribution, Є to the margin of error, and *n*_+*i*_ to the sample size of the *i* stratum, where *i* = 1, …,8 and *h* = 8. The standard deviation 
[figure not shown]
 of the population in each stratum was derived from the information.

The sample size of the patient group was calculated according to the level of significance and the margin of previously selected errors as *n*_+_ = 47. The final target sample size for the stroke patient group was 

, accounting for a 15% drop-out rate. (Table 1)

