### Data collection

2.5

The data will be collected through a participant survey and through investigator measurements at baseline (on visit 1) and at specified follow-up times (on visits 2 to 7). (Table 3)

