### Adverse events

2.10

The investigators will record adverse events and unexpected responses. Adverse events will be reported by the participants and will be evaluated by the investigators as mild, moderate, or severe according to the World Health Organization Draft Guidelines for Adverse Event Reporting and to Spilker's criteria. When severe adverse event happens, the trial participant will discontinue the trial.

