## Discussion

3

The outcome measures of this study will be the differences and changes in the radial artery pressure pulse, in the blood vessel properties, and in the physiological data obtained during the treatment of patients with hemiplegia caused by stroke. The changes in the artery pressure pulse, in the blood vessel properties, and in the physiological data will be compared.

These results can provide information about physiological and hemodynamic mechanisms. They will also help to clarify whether the radial artery pressure pulse wave can be used to evaluate the result of stroke treatment objectively. This study's findings will be scientifically relevant, as they will allow us to quantify the degree to which the PWRA is related to the reduction in daily physical activities in stroke patients with hemiplegia, and to analyze the changes over time. To our knowledge, this will be the first study to compare the PWRA on the affected side and on the normal side of stroke patients with hemiplegia. It will also show the relationship between hemiplegia and the PWRA over a follow- up period of 6 months.

Data on the changes in the pulse wave characteristics of the radial artery and on the course of these changes over time in stroke patients with hemiplegia are currently scarce and inconclusive. To achieve external validity and to provide a standardized Korean Medicine diagnosis system for stroke and to benefit evidence-based medicine, further studies need to assess these factors quantitatively and qualitatively. The present study hopes to contribute evidence to help clarify some of these issues. Its results will be available in February 2019.

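### LOCF is the only stated method for missing data; it would shrink the estimated change in rAIx if rAIx is still moving when participants leave

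*Protocol article*

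**What the plan says.** All references are to the protocol article.

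- **Missing data (2.8 Statistical analysis):** "The last observation carried forward (LOCF) method will be used to impute the missing data". No outcome, visit or analysis set is exempted, and no other method is named.
- **Primary outcome (Abstract, Methods/design):** "The primary outcome of this study will be the differences and changes in the radial augmentation index". Change is therefore part of the primary outcome, alongside differences.
- **Visits (2.5 Data collection; Discussion):** baseline is visit 1, follow-up is at visits 2 to 7, and the Discussion gives a 6-month follow-up.
- **Drop-out (2.4.4 Sample size):** the case-group target is described as "accounting for a 15% drop-out rate".
- **Early exit (2.10 Adverse events):** "When severe adverse event happens, the trial participant will discontinue the trial".
- **Analysis of change (2.8):** within-group comparisons use either RMANOVA or a linear mixed-effects model, with no rule for choosing. Dunnett's test compares later time points with baseline.
- **Sensitivity analysis (2.8):** the only one named is the full analysis set against the per-protocol set.

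**The concern.** LOCF assumes that a participant's value stays where it was at the last attended visit. Change after that point is what the study sets out to measure, in patients who had a stroke within the past 6 months and are in rehabilitation. If rAIx follows a steady course, each filled visit holds a value closer to baseline than the true one. The mean change at late visits, and the Dunnett contrasts built on it, then come out too small.

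At stake is the study's answer on whether the radial pulse wave tracks recovery. Comparing the full analysis set with the per-protocol set does not guard against this: it varies who is analysed, not what is assumed about missing values.

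**Working it through.** **1. The plan's own figure.** Inflating n = 47 for 15% drop-out gives 47/(1 − 0.15) = 55.3, rounded up to 56. This matches the stated case group, so 15% is the plan's working rate, or about 0.15 × 56 = 8.4 case patients. The 47 cannot be checked, because its equation and stratum table are not shown.

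**2. Loss under LOCF, drop-out unrelated to outcome.** Number the visits k = 0 (visit 1) to k = 6 (visit 7). Let f(k) be the share of the total mean change reached by visit k, and d the drop-out share.

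Share of the change lost at visit 7 = d × mean of [1 − f(last visit attended)]

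The rate d = 0.15 comes from 2.4.4. The course f and the timing are assumptions.

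- *Linear course, f(k) = k/6, leaving spread evenly over visits 2 to 7:* mean of 1 − f = (6 + 5 + 4 + 3 + 2 + 1)/36 = 0.583. Loss = 0.15 × 0.583 = 8.75%.
- *Front-loaded course, f(k) = (1 − e^(−k/2))/(1 − e^(−3)), same timing:* mean of 1 − f = (1 + 0.586 + 0.335 + 0.182 + 0.090 + 0.034)/6 = 0.371. Loss = 0.15 × 0.371 = 5.6%.
- *All leave straight after baseline:* 1 − f = 1. Loss = 15%, the ceiling for a steady course.
- *Only visit 7 missed:* loss = 0.15 × 1/6 = 2.5% (linear) or 0.15 × 0.034 = 0.5% (front-loaded).

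For an assumed drop-out of 5% to 25%, the loss runs from about 0.2% (5%, front-loaded, only visit 7 missed) to 25% (25%, all leaving after baseline).

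**3. Simulation with 56 patients and 7 visits.** All inputs other than n, the number of visits and the 15% rate are assumed. The true change is 0.50 SD in size and linear, unless stated as zero.

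*Model A: within-person correlation 0.6, about 15% drop-out, signs as simulated (true change −0.50 or 0).*

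| Setting | LOCF | Mixed model, observed visits |
|---|---|---|
| Change −0.50, random drop-out | −0.453 | −0.498 |
| Change −0.50, drop-out depends on baseline value | −0.459 | −0.515 |
| No change, random drop-out | −0.001 | −0.003 |

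*Model B: intercept variance 0.7, residual variance 0.3, slope SD 0.4, drop-out hazard about 2.7% per visit (1 − 0.973^6 = 15%), optionally raised for patients with less progress.*

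| Setting | LOCF | Loss | Likelihood analysis, observed visits |
|---|---|---|---|
| Random, 15% | 0.454 | 9% | 0.498 |
| Moderate dependence, 16% | 0.417 | 17% | 0.503 |
| Strong dependence, about 15% | 0.382 | 24% | not run |
| Strong dependence, 24% | 0.331 | 34% | 0.516 |

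A separate rerun of the first, second and fourth settings of Model B gave LOCF means of 0.456, 0.418 and 0.322.

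**4. Standard errors.** In that rerun, the model-based and empirical standard errors of the LOCF change from baseline were 0.114 and 0.114, 0.120 and 0.120, and 0.132 and 0.131.

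**The case against.** The strongest reply is that the bias is conditional and modest. The study is exploratory, and the Discussion calls existing data on these changes scarce and inconclusive. If rAIx does not move on average and drop-out is random, LOCF leaves the mean unbiased, as Model A shows. At 15% random drop-out the shortfall is about 0.03 to 0.04 SD (LOCF means 0.472 front-loaded and 0.456 linear, against 0.50), beside a standard error of about 0.114 SD. Power for the change falls only from 0.99 to 0.98. Baseline comparisons, between cases and controls and between sides, are also primary and are untouched. All of this stands. It limits the severity but does not make LOCF suitable for an outcome defined as change.

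A second reply is that the article is condensed. Table 3 is not shown, so which visits measure rAIx, and whether controls are followed, cannot be checked. Nor does the article say whether LOCF-filled data would feed the mixed model. This also stands, but the LOCF sentence is a stated choice without limits, not a detail left open.

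A reader might infer more than the documents support:

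- *That a third of the change would be lost.* The 34% case needs 24% drop-out strongly tied to progress; the plan gives 15% and says nothing about dependence.
- *That LOCF makes the result look too certain.* For change from baseline, the standard errors in step 4 agree. Other analyses of the filled data could differ, but this has not been shown.
- *That RMANOVA is why LOCF was chosen.* The article gives no reason for LOCF.
- *That the discontinuation rule in 2.10 must change.* It is a route to early exit linked to health, but no event rate is given, so its contribution cannot be sized. Correcting the analysis does not depend on it.

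**Conclusion.** The point holds as a conditional one and should be fixed before analysis; it is not a fatal flaw. Applied as written, LOCF pulls a steady change in rAIx toward zero whenever participants leave while rAIx is still moving. At the planned 15% drop-out, unrelated to outcome, the loss is about 6% to 9% with evenly spread leaving and at most 15%. It is about 17% to 24% under the assumed settings in which leaving depends on progress. These sizes rest on an assumed course, timing and dependence, and the simulated ones also on an assumed 0.50 SD change and assumed variances. The documents do not support saying that the rAIx result will be biased, only that the stated method would bias it under the conditions the study expects. No named sensitivity analysis would reveal this.

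**What to change.** In section 2.8:

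- Make the linear mixed model already named there the primary analysis of change in rAIx, with visit as a factor and a participant effect, fitted by REML to all observed visits without imputation.
- Remove RMANOVA as the alternative.
- Keep LOCF at most as a sensitivity analysis, labelled as such.

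The change is to analysis wording only; no extra participants or visits are needed. The downside is that the mixed model relies on data being missing at random given what was observed, which cannot be verified. Its estimate may also vary slightly more: in Model A with random drop-out and a true change of −0.50, its SD across runs was 0.123 against 0.114 for LOCF.

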### Data handling

2.9

The investigators will enter the information required by the protocol into case report forms (CRFs). Non-obvious errors or omissions will be entered into data query forms that will be returned to the investigational site for resolution. The data from all of the centers will be gathered and summarized into baseline demographic characteristic observations. The participant information will be treated confidentially. The final data set will be accessible by the principal investigator.

### Adverse events

2.10

The investigators will record adverse events and unexpected responses. Adverse events will be reported by the participants and will be evaluated by the investigators as mild, moderate, or severe according to the World Health Organization Draft Guidelines for Adverse Event Reporting and to Spilker's criteria. When severe adverse event happens, the trial participant will discontinue the trial.

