### Study design

2.1

This study was conceived as a prospective and observational study to explore the differences and changes in radial artery pulse waves during the treatment of patients over 50 years old suffering from hemiplegia caused by stroke. As a matched case-control study, it aims to compare the pulse waves in the radial arteries of participants with hemiplegia caused by stroke with those of healthy participants. The study will be carried out at the Wonkwang University Gwangju Hospital Clinical Trial Center of Gwangju, in the Republic of Korea.

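### Severe adverse events end participation in an observational study, so later rAIx values go uncollected and LOCF fills them, which can bias the change part of the primary outcome

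*Protocol article*

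**What the plan says.** Section 2.10 (Adverse events) grades events by intensity; they "will be evaluated by the investigators as mild, moderate, or severe". It then sets the rule: "When severe adverse event happens, the trial participant will discontinue the trial". No exception is given, relation to a study measurement is not mentioned, and nothing is said about measurement afterwards.

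Section 2.1 describes the design: "This study was conceived as a prospective and observational study to explore the differences and changes in radial artery pulse waves". Section 2.5 has a baseline visit and follow-up visits 2 to 7, and the Discussion gives a follow-up of 6 months. The abstract defines the endpoint: "The primary outcome of this study will be the differences and changes in the radial augmentation index".

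Section 2.8 handles gaps in one sentence: "The last observation carried forward (LOCF) method will be used to impute the missing data". Sensitivity is to come from comparing the full analysis set (FAS) with the per-protocol set; no other treatment of missing values is named. Within-group change is to be analysed by repeated-measures ANOVA or a linear mixed-effects model, and "The time point difference in contrast with the baseline will be examined with Dunnett's test".

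**The concern.** Leaving the study and stopping a procedure are different things, and section 2.10 does not separate them. In an observational study there is no assigned study treatment to stop, so leaving the trial mainly means that the remaining visits do not take place. Because the trigger is a severe health event, the loss is related to health state by design.

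Section 2.8 then fills the gap with the last value before the event. A participant whose rAIx moved afterwards is analysed as if it had stayed still. Comparing the FAS with the per-protocol set does not test this, because the FAS contains the carried values and neither set contains the missing ones.

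At stake is the change component of the primary outcome, and with it the stated aim of learning whether the radial pulse wave can be used to judge the result of stroke treatment. That aim needs follow-up on patients who do badly as well as on those who do well.

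**Working it through.** **Inputs from the article.** 56 cases and 28 controls (section 2.4); 47 cases before drop-out and a 15% drop-out allowance (section 2.4.4); visits 1 to 7 (section 2.5); LOCF (section 2.8).

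**The plan's own figure.** 47 / (1 − 0.15) = 55.3, rounded up to 56; controls 0.5 × 56 = 28; total 84. This reproduces. The 47 cannot be re-derived because the equation and stratum table are not shown, and this point does not dispute it.

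**Inputs not in the article.** There is no severe-event rate, no expected change in rAIx and no SD. The following are therefore assumptions:
- k = number of the 56 cases withdrawn under the rule, from 1 to 8. The top is 8/56 = 14.3%, close to the whole 15% allowance.
- d = mean gap between the true later change and the carried-forward change, in SDs of change, from 0.5 to 1.0, all in one direction.

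**Size.** Bias in mean change = (k/56) × d. Standard error (SE) of a mean change over 56 cases = 1/√56 = 0.134 SD, taking the SD as unchanged by the imputation. Coverage of a nominal 95% interval = Φ(1.96 − b) − Φ(−1.96 − b), with b = bias/SE.

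| k | d | Bias (SD) | Bias/SE | Coverage |
|---|---|---|---|---|
| 1 | 0.5 | 0.009 | 0.07 | about 95% |
| 1 | 1.0 | 0.018 | 0.13 | about 95% |
| 5 | 0.5 | 0.045 | 0.33 | about 94% |
| 5 | 1.0 | 0.089 | 0.67 | about 90% |
| 8 | 0.5 | 0.071 | 0.53 | about 92% |
| 8 | 1.0 | 0.143 | 1.07 | about 81% |

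**Direction.** Let D be the mean 6-month change in the other cases, f = k/56, and t the share of their own change that withdrawn cases had reached at their last visit.
- If withdrawn cases would have changed like the rest, LOCF shifts the mean by −f(1 − t)D. For t = 0 this is −1.8% of D (k = 1), −7.1% (k = 4) and −14.3% (k = 8). For t = 0.5 it is −0.9%, −3.6% and −7.1%. The change is understated.
- If they would have moved the opposite way (−D), the true mean is (1 − 2f)D and LOCF gives (1 − f − ft)D. For k = 8 the true mean is 0.714D; LOCF gives 0.857D at t = 0 (+0.143D) and 0.786D at t = 0.5 (+0.071D). The change is overstated.

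The sign depends on what would have happened after the event, which the plan arranges not to observe.

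**Share due to this rule.** If only a fraction a of the withdrawn cases could still have been measured, the avoidable bias is a × (k/56) × d. For example, if 4 of 8 could have been measured and d = 1.0, it is (4/56) × 1.0 = 0.071 SD, not 0.143 SD.

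**What is untouched.** Comparisons made at baseline, between cases and controls or between the affected and less affected side, precede any withdrawal.

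**The case against.** The strongest reply is that one sentence in a condensed article is being asked to carry too much. Section 2.10 does not say whether the event must be related to a study measurement, and the full protocol may deal with relatedness and with follow-up after withdrawal. That silence is not itself a fault. But the sentence is a stated rule, not an omitted detail, and as worded it takes the participant out of the trial.

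Second, the study is observational, but treatment does run alongside it: cases must be able to follow the institution's stroke pathway (section 2.4.2), and the aim refers to change after physiotherapy. This stands. The point needs only that the study itself assigns no treatment.

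Third, part of the computed bias belongs to LOCF. If exit depended only on values already observed, the mixed model named in section 2.8, fitted without carried values, would deal with it. That also stands. What remains due to section 2.10 is the part that depends on values after the event, which no model recovers if they are never collected.

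Fourth, a reader might infer more than the article supports:
- **That the sickest patients are removed and look better than they are.** A severe adverse event need not be neurological worsening, and the exclusion criteria remove much serious disease, so such events may be few.
- **That early values stand in for late ones.** LOCF carries the last value, which may itself be late.
- **That cases lose more data than controls.** No event rates are given, and the visit schedule (Table 3) is not shown, so the controls' visits cannot be seen.
- **That a link between worsening and rAIx is weakened by a known amount.** Nothing in the article allows that to be calculated.

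**Conclusion.** The concern holds in a limited form. Section 2.10 as worded ends data collection after a severe event in an observational study, and section 2.8 fills the lost visits with the last pre-event value. This can bias the estimated change in rAIx.

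Under the stated assumptions the bias runs from about 0.01 to 0.14 SD of change (0.07 to 1.07 standard errors). It is negligible if one case is affected, and material only if severe events use up much of the drop-out allowance and the later change differs markedly. It is zero if no severe event occurs or rAIx stays flat afterwards. Bias in a particular direction, or of a particular size, is not established. The change is still worth making before data are collected, because values never taken cannot be restored at analysis.

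**What to change.** In section 2.10, separate stopping a study procedure from leaving follow-up. State that after a severe adverse event the scheduled rAIx and other outcome measurements continue where the participant agrees and the treating physician does not object. Record the date and reason of any loss that still occurs, and report such losses by group. Care decisions stay with the treating physician; the change concerns data collection only.

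In section 2.8, analyse the observed data with the linear mixed-effects model already named there, instead of carrying the pre-event value forward. The two changes belong together: the model alone cannot supply uncollected values, and collection alone leaves LOCF in place for the remaining gaps. Disability scores taken from the medical record would help to describe lost patients but would not recover rAIx.

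The cost is a short amendment to section 2.10, a matching line in the consent form, a wording change in section 2.8, and a few visits that are already in the schedule. No new procedure is needed and the sample size is unaffected.

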### Monitoring

2.11

Monitoring will be conducted regularly by a clinical research monitor. At the time of the visit, the monitor will check the original patient record, medical device management record, and data archive (e.g., study file).

